## 2.5 Exclusion Criteria

- Non-Emirati patients or patients without full insurance coverage.
- Patients with severe or symptomatic hypo- or hypermagnesemia and/or hypo- or hyperkalaemia, metabolic acidosis or hypophosphatemia with or without proximal renal tubular acidosis and Fanconi syndrome.
- Patients with prolonged hypokalaemia with surreptitious diuretic use, laxative abuse, eating disorders or primary aldosteronism.
- Patients receiving medications that may cause drug-induced acute renal failure during the observational period and may be implicated in hypomagnesaemia (e.g. aminoglycoside antibiotics, cyclosporine, amphotericin B, cisplatin, pentamidine and foscarnet).
- Patients who have undergone bariatric surgery within the past two years or other gastrointestinal surgeries that induce chronic malabsorption.
- Pre-menopausal women who are nursing or were pregnant within the last 12 months.
- Blood dyscrasias or any disorders causing haemolysis or unstable red blood cell population (e.g., malaria, babesiosis, haemolytic anaemia).
- Stage 4 or 5 CKD patients, with a severe reduction in glomerular filtration rate, kidney failure or dialysis, defined as GFR ≤ 29 ml/min or albumin/creatinine ratio ˃ 30 mg/mmol as baseline value.
- High cardiovascular risk, defined as 10-year predicted atherosclerotic cardiovascular disease (ASCVD) risk ≥7.5% by Pooled Cohort Equation or Framingham risk score ≥20%, or cardiac surgery, or angioplasty within the last 12 months or any diabetic macrovascular complications as defined in our definition.
- Indication of liver disease, defined by serum levels of either alanine aminotransferase (ALT), aspartate aminotransferase (AST) or alkaline phosphatase (ALP) above 3 x upper limit of normal as defined at the beginning of the study or within the last 12 months.
- Medical history of cancer and/or treatment for cancer within the last five years, or immune compromised patients.
- Treatment with systemic steroids or change in dosage of thyroid hormones within the last 12 months after starting the study or any other uncontrolled endocrine disorder.
- Patient with communication barriers that may affect obtaining patient adherence, receiving diet, exercise counselling or consent signing, and include:
- a. Patients with severe emotional distress.
- b. Patients who are unable to use mobile applications or access the internet for any reason.

## 2.6 Randomization

Randomization processes will be performed by a computer-generated random number in Excel Microsoft Office to generate an allocation sequence for each participant in the intervention and control group by the equation (=UNIQUE(RANDARRAY(239,1,1,300,FALSE)), with allocation concealment by sequential numbering representing the participant’s turn in joining the study. All patients identifying data will be removed to conceal randomisation and minimise predictability of the generated random sequence.

Each patient will be assigned a code documented in the consent form and the data entry sheet by the principal investigator, and this information will be saved in a password-protected file. Participants in the intervention group will be identified electronically one week before the next refill schedule or follow-up visit. The control group will continue to receive routine care provided in the clinic during the study period without any interfere in their follow-up appointments.

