## 2.3 Study Participants

The study will recruit Emirati patients previously diagnosed with T2DM from the endocrinology or chronic disease (CDC) clinics, who have will match the research inclusion criteria and have been taking the same diabetes medications for 12 weeks before the study with regular follow-up schedules in the previous year. Eligible patients will be randomized and blinded to the intervention and control groups.

The patients will be included in the analysis are those whose records are available in Salamtak (electronic medical record system operated by the Salamtak platform). At the end of the study, those with a medical history of cancer, chronic liver disease, high cardiovascular risk (defined as a 10-year predicted atherosclerotic cardiovascular disease (ASCVD) risk of ≥7.5% using the pooled cohort equation or a Framingham Risk Score of ≥20%), cardiac surgery within the last 12 months or any diabetic macrovascular complications will be excluded. Moreover, patients will be excluded either if they withdraw from the study or have a missed follow-up data including missed laboratory tests at the end of study period as per study protocol.

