Moreover, the control group will have their HbA1c levels recorded at least twice yearly (at initial and exit visits) in patients with stable glycaemic control meeting the treatment goals and quarterly in patients not meeting the treatment goals, which will be at the discretion of the attending physician [40]. Other laboratory tests will be performed twice yearly (or more frequently as per the physician’s request), and any major adverse cardiac events, emergency room visits or hospitalisations will be recorded and compared with baseline data.

The intervention group will receive multi-factorial interventions and assessments at initial visit and at each follow-up visit every 3 months after enrolment in the study. The multi-factorial interventions composed of the three below approaches: medication adherence counselling with medication therapy management program, diet and exercise counseling, and serum sodium, potassium and magnesium optimization (Figure 1).

- Adherence and MTM assessment.
- Diet and exercise assessment.
- Clinical outcomes and electrolyte level assessment.

Close-out

12-month visit

12-month visit

- Adherence counselling and MTM.
- Diet and exercise intervention.
- Multifactorial interventions with electrolytes level optimization.

Interventions

6-month visit

3-month visit

1-month visit

9-month visit

- Baseline laboratory tests, Na/K/Mg levels .
- Medication adherence questionnaire.
- Diet and exercise assessment.

Pre-assessment

Initial visit

Initial visit

Eligibility – Inclusion - Randomisation (1:1)

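### Section 2.6 generates random decimals with no rule that assigns an arm, its concealment does not hide the next assignment, and the blinding claimed in Section 2.3 does not fit the design

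*Protocol*

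**What the plan says.** Section 2.6 uses an Excel formula "to generate an allocation sequence for each participant in the intervention and control group". Figure 1 in Section 2.8 labels the step "Randomisation (1:1", that is, equal allocation.

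The formula and the concealment appear in one sentence of Section 2.6: "by the equation (=UNIQUE(RANDARRAY(239,1,1,300,FALSE)), with allocation concealment by sequential numbering". The numbering is explained there as "allocation concealment by sequential numbering representing the participant’s turn in joining the study". A second safeguard is offered: "All patients identifying data will be removed to conceal randomisation and minimise predictability of the generated random sequence".

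On codes, the section adds: "Each patient will be assigned a code documented in the consent form and the data entry sheet by the principal investigator". Their storage is covered by one clause only, namely that "this information will be saved in a password-protected file".

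Section 2.3 says: "Eligible patients will be randomized and blinded to the intervention and control groups".

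Section 2.10 plans 180 participants, 90 per group, and gives 184 in total for the HbA1c outcome.

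**The concern.** Random, concealed assignment supports every between-group comparison in Section 2.10. Two things are needed: a rule that takes each list position to an arm, and a barrier that keeps that arm unknown until the patient is irrevocably in the trial. Section 2.6 claims both and describes neither.

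If someone who recruits or assesses patients can see the next assignment, motivated patients can be entered when the intervention is next and others deferred. Adherence, diet and HbA1c would then differ between arms for reasons other than the programme, and the direct two-group tests in Section 2.10 would not reveal it. The adherence questionnaire and the food logs are self-reported, so a mistaken claim of blinding also misstates how exposed those outcomes are to expectation.

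**Working it through.** **1. What the formula returns.** Its arguments (Section 2.6) are 239 rows, 1 column, minimum 1, maximum 300 and integer flag FALSE. FALSE gives decimals. UNIQUE removes duplicates, but random decimals practically never tie: in 5,000 simulated runs all 239 of 239 values were kept. The output is 239 distinct decimals and no group labels.

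**2. Can the stated 1:1 be reproduced?** No. It needs a rule from decimal to arm, and none is given. Two rules that could be assumed lead to different lists:
- Cut at the midpoint, (1 + 300)/2 = 150.5: each patient is assigned independently, so 1:1 holds only in expectation.
- Rank and split: 239/2 = 119.5, so the full list divides 120 and 119. If only the first 180 positions are used, the arm with 120 positions receives 84 to 97 patients (95% range, hypergeometric with 239, 120 and 180).

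Either could be defended. The point is that the text does not choose.

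**3. List length.** 239 − 180 = 59 and 239 − 184 = 55. The surplus is unexplained.

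**4. What each stated safeguard does.**

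| Stated safeguard | What it achieves | What it leaves open |
| --- | --- | --- |
| Sequential number by order of joining | Identifies the next list position | Does not hide the arm at that position |
| Removal of identifying data | Confidentiality | Does not affect who can see the sequence |
| Code assigned by the principal investigator, kept in a password-protected file | Secures the patient codes | Is not said to hold the sequence or to keep it from recruiting staff |

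No holder independent of enrolment is named, and no release step is described.

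**5. When assignment becomes known.** Figure 1 places randomisation after eligibility and inclusion. Section 2.6 has intervention patients flagged electronically a week ahead of a coming refill or follow-up visit. Section 2.8.1 has them enter the pharmacist programme at the first visit, with a counselling session then. Section 2.8 puts the baseline adherence, diet and exercise assessments at that same initial visit. Table 4 in Section 3 dates the first intervention phase three months after entry. These statements do not fix one moment of disclosure, and they do not establish that baseline assessment comes before it.

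**6. Blinding.** Both arms receive baseline medication counselling and basic diet advice (Sections 2.8.1 and 2.8.2). Only the intervention arm receives the repeated pharmacist sessions with follow-up calls, the medication booklet, the structured diet sessions and the monthly coaching calls. Patients and the staff delivering these will know the arm.

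**The case against.** The best defence has four parts.

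- **Order of events.** Figure 1 puts randomisation after inclusion, and the electronic flagging in Section 2.6 suggests that the arm is revealed after entry. This stands as evidence of intent. It does not amount to concealment, because Section 2.8.1 starts the programme at the first visit and nothing says who could see the list before then.
- **Unpredictability.** Random decimals cannot be guessed, and untied decimals make a normal sort key. This also stands. A reader might infer that the sequence itself is predictable, or that the principal investigator held it and steered patients. The documents support neither. They say that the principal investigator assigns codes and that a doctor seeks consent (Section 2.7); they do not say who held the sequence, and they report no misuse.
- **Reproducibility.** A live RANDARRAY cell redraws at recalculation, so a reader might infer that the list cannot be audited. The protocol does not say whether the values were saved, so that conclusion goes too far. What can be said is that no fixed list is described.
- **Chance imbalance.** Simple randomisation is a legitimate 1:1 method. Even a split of 80 and 100 has an effective size of 4 × 80 × 100/180 = 177.8 against 180, a loss of about 1.2%. Figures for unequal arms under an assumed coin-flip rule, or for duplicates under a whole-number version of the formula, describe procedures that the protocol does not state and do not measure this problem.

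The blinding sentence may be loosely worded and may mean that the assignment was made blind. Even so, as printed it claims something about patients that does not hold.

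**Conclusion.** The point holds in this form: the stated formula does not allocate, the stated concealment does not conceal, the timing of disclosure is inconsistent, and blinding is not a property of this design. This is not detail that may be left to a statistical analysis plan, because the protocol states the method itself and states it wrongly.

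The effect on results cannot be sized. It could be nil, if the list was in fact kept from those enrolling and assessing patients, or material if it was not; the documents do not allow a choice between the two. The loss from unequal arms is negligible. The conclusion assumes only that the formula behaves as its arguments indicate and that no allocation procedure is described elsewhere in the protocol.

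**What to change.** In Section 2.6, state the rule that takes each list position to an arm, and say that a 1:1 list is generated once and stored as fixed values. Explain its length against the planned 180 or 184. Name by role an existing staff member who takes no part in enrolment or baseline assessment to hold the list, and release each assignment only after consent and baseline assessments are recorded. No particular block size is required. Reconcile Sections 2.6, 2.8.1 and Table 4 on when assignment is disclosed and the programme begins. In Section 2.3, replace the word blinded with open-label.

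Before enrolment this costs protocol wording and a short task in a spreadsheet, with no added staff or patients. Table 4, however, schedules recruitment for July to September 2021, and the reference list cites a web page accessed in January 2024, so enrolment is probably complete. In that case a new list cannot be applied. The protocol and the trial report should then state how numbers became groups, who held the list and when assignments were disclosed, and should correct the concealment and blinding claims. That costs only the writing, but analysis cannot repair selection at entry if the account shows that the list was visible.

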## 2.7 Patient Consent

At the physician’s office, the doctor will discuss the possible participation of the eligible patient in the study, and if satisfied, the participant will sign the consent form (Appendix 1) and receive a copy of it along with the study information sheet (Appendix 2).

The trial will be submitted and monitored by SEHA Research Ethics Committee (REC) after approval. The results will be communicated to the SEHA REC in the terminal report and to the public in a peer-reviewed journals. Moreover, the physicians from the Oud Al-Touba clinic will have access to the clinical trial protocol and research results, in a way that protects patient’s confidentiality, to advance medical research and understanding, and any modifications in study protocol (if needed) will be submitted to SEHA REC for approval.

Patients’ confidentiality will be maintained during the study, and all de-identified protected health information will be recorded electronically and saved securely by password protection, limiting the access to authorised research personnel only and SEHA REC for auditing and monitoring purposes during the study period.

Authorship agreement to declare the intellectual contributions of the research team, origin of the research and accountability of any published information was written and will be reviewed by the research team before publication.

The research is not sponsored by any company, and the researchers have declared that they have no known notable financial interests that would reasonably appear to affect the research. Although participants will not be compensated for their extra time spent during interviews or for any inconvenience that may result from taking extra medications or blood tests every 3 months, they will grant prioritised access to physician’s appointments, including dietician’s visits. Furthermore, they will grant direct access to our cardiologist in case of any harm from prescribing medicines or abnormal laboratory results, without any additional cost. Moreover, a 12-h counselling hotline will be available during and after the study follow-up period to answer any queries or report any side effects.

## 2.8 Study Procedures

Eligible participants will sign the consent form at the physician’s office, and laboratory results will be recorded as baseline data. If the patient’s medical record does not contain recently updated laboratory tests from the previous three months, laboratory tests will be scheduled for blood sample collection in the clinic and tested in Abu Dhabi Health Services Company (SEHA) central laboratory, and the same process will be performed at the conclusion of the follow-up period after 12 months. Laboratory tests in the study protocol included gylcated hemoglobin A1c (HbA1c), estimated Glomerular Filtration Rate (eGFR), complete blood count, electrolyte panel including potassium and magnesium levels, serum creatinine levels, and albumin/creatinine ratio.

Laboratory and clinical assessments in the study protocol included BP measurement and laboratory tests HbA1c level, low-density lipoprotein cholesterol (LDL-C) level, complete blood count, electrolyte panel including K and Mg levels, eGFR, serum creatinine level, and albumin/creatinine ratio. BP measurements and laboratory tests will be performed according to the standard procedures for BP measurement and blood sample withdrawal at the clinic.

In addition, each participant in both groups will undergo individual assessments at initial visit and study exit including medication adherence by clinical pharmacist and diet and exercise assessment by specialized dietician.

During the study period, the control group will receive the usual care provided in the clinic including the routine follow-up and clinical assessments (as needed). The routine usual care will include follow-up schedule every 3 months with the treating physician, vital signs monitoring in the visited clinic, physician consultation, any additional investigational services or laboratory tests requested by the treating physician depending on each patient’s condition, patient counselling at the pharmacy counter, dietitian counselling service if requested by the patient or referred by the treating physician, and a call reminder from the clinic call centre 3 days before the appointment.

Moreover, the control group will have their HbA1c levels recorded at least twice yearly (at initial and exit visits) in patients with stable glycaemic control meeting the treatment goals and quarterly in patients not meeting the treatment goals, which will be at the discretion of the attending physician [40]. Other laboratory tests will be performed twice yearly (or more frequently as per the physician’s request), and any major adverse cardiac events, emergency room visits or hospitalisations will be recorded and compared with baseline data.

The intervention group will receive multi-factorial interventions and assessments at initial visit and at each follow-up visit every 3 months after enrolment in the study. The multi-factorial interventions composed of the three below approaches: medication adherence counselling with medication therapy management program, diet and exercise counseling, and serum sodium, potassium and magnesium optimization (Figure 1).

- Adherence and MTM assessment.
- Diet and exercise assessment.
- Clinical outcomes and electrolyte level assessment.

Close-out

12-month visit

12-month visit

- Adherence counselling and MTM.
- Diet and exercise intervention.
- Multifactorial interventions with electrolytes level optimization.

Interventions

6-month visit

3-month visit

1-month visit

9-month visit

- Baseline laboratory tests, Na/K/Mg levels .
- Medication adherence questionnaire.
- Diet and exercise assessment.

Pre-assessment

Initial visit

Initial visit

Eligibility – Inclusion - Randomisation (1:1)

**Intervention Group**

**Control Group**

Enrollment

Figure 1: One-year, randomised control study.

FMPR= Fixed medication possession ratio, K = Potassium, Mg = Magnesium, MTM = Medication therapy management.

### 2.8.1 Medication Adherence and Medication Therapy Management (MTM)

We will examine a multi-factorial pharmacy-led interventions protocol (MPIP) that aims at maximizing patients’ adherence. Patients in the intervention group will receive comprehensive patient counselling designed to improve participant understanding and enhance appropriate use of medications, with a follow-up phone interview within 2 weeks after each follow-up visit. Moreover, we will examine medication therapy management (MTM) intervention as distinct group of services provided to each participant in the intervention group as part of MPIP and occur in conjunction with medication adherence counseling.

MTM encompasses of several activities including performing comprehensive medication reconciliation and review to identify as well as resolve any medication related issues or adverse events, modifying or optimizing medication therapy in coordination with health care providers, monitoring, evaluating or requesting necessary laboratory and assessments of participants health status, and finally formulating a pharmaceutical care plan to evaluate and monitor patient’s compliance and response to therapy. In addition to other support services such as medication booklet and mobile application to optimize patient clinical outcomes to their therapeutic regimens.

Intervention procedure:

At baseline, participants in both groups will receive medication counselling by a clinical pharmacist as part of the usual care provided in the clinic, and baseline assessment of medication adherence will be performed using a validated medication adherence questionnaire (Appendix 3) [41]. Participants will be instructed to report any possible side effects or factors that may affect their medication adherence, and to reveal any modifications in lifestyle activities or eating habits during the study.

Participants in the intervention group will join the MPIP program on their first visit and will receive two multifactorial interventions: medication adherence counselling and medication therapy management, as detailed below.

1. Medication Adherence Counselling

Each participant in the intervention group will receive a 15- to 30-min counselling session at the initial visit and each scheduled follow-up visit which will occur every 3 months. During these sessions, the pharmacist will assess medication adherence with a validated adherence questionnaire (Appendix 3) and counsel the patients on the importance of medication adherence on clinical outcomes. The barriers to medication adherence will be identified, discussed with the patient, and resolved as much as possible. Finally, the patient will be provided with two or three months of medication supply, and the medication refill date will be documented for medication adherence calculation using the medication possession ratio (MPR) [42, 43].

After each visit, each participant in the intervention group will receive a 15-minute follow-up phone interview within two weeks for adherence reinforcement and to address any non-compliance issues or medication side effects. Moreover, they will be scheduled for their next medication refill and follow-up visits in the clinic appointment system. Appointments will be scheduled at months 3, 6, and 12 from the initial visit according to the patient’s preferred date, and they will receive a reminder phone call three days before the next visit from the clinic call centre.

Medication adherence will be evaluated using two techniques during the follow-up period: calculating the medication adherence possession ratio and the medication adherence questionnaire scores.

1. Medication Adherence Possession Formulas

In this study, we will use three formulas to calculate medication adherence from patients’ medication refills recorded in Salamtak:

1. Total Fixed Medication Possession Ratio (MPRt)

A fixed medication possession ratio (MPR) formula will be used to measure total (composite) adherence to all medications (MPRt) [44, 45]. The MPRt will be calculated for three chronic regimens including antihyperglycaemic, antihypertensive and antihyperlipidaemic regimens.

For the total MPRt, no regimen-specific MPR (MPRs) will be measured. It is calculated by summing the days’ supply of medication per prescription, then dividing by the number of days of patient follow-up, using a fixed follow-up period of 365 days (12 months) as a constant denominator, adjusted to hospital stay if the participant was admitted during the follow-up period (Figure 2).

$$\text{MPR}\text{t}\text{ }\text{=}\frac{\sum_{i = 0}^{End of follow-up period} \text{Days of supply Rxi}}{\text{Days of follow-up period}}$$

$\text{MPR}\text{t}\text{ }\text{=}$

Figure 2: Fixed total medication possession ratio (MPRt) calculation

For the above example, if the patient had a medication supply equal to 345 days (90 days + 75 days) during the fixed follow-up period of 365 days, the MPRt calculated as 345/365 = 0.95.

1. Regimen-specific Medication Possession Ratio (MPRs)

Regimen-specific MPR (MPRs) will be calculated for all three regimens (antihyperglycaemic, antihypertensive, and antihyperlipidaemic), whether any or all were contained in the patient’s medication profile [46, 47].

The denominator for MPRs also covers the follow-up period of 12 months but will be calculated based on the last refill date for a specific medication regimen (for any medication class) minus the first refill date for any medication in the regimen, even if this medication was in a different class from the medication used in the last refill. In addition, medications within the same regimen will be considered interchangeable (even if they belonged to different medication classes).

$$\text{MPRs}\text{ }\text{=}\frac{\sum\text{Days of supply of }\text{medication}\text{ in a regimen}}{\text{Last refill date‐First refill date} \left( \text{for specific regimen} \right)}$$

Of note, for both types of MPR (MPRt and regimen-specific MPRs), if the patient had refilled medication prior to the date of joining the study, MPR will be calculated from the date of signing the consent, excluding the supply from the last prescription or medication refill and will be capped at 1, and medication adherence (either MPRt or MPRs ) will be calculated after 12 months of follow-up [42].

The standard adherence threshold of 0.80 MPR will be used as a lower bound for mediation adherence [45], with MPR = 1 indicating perfect adherence, MPR < 0.80 indicating patient non-adherence, and MPR= 0 indicating no adherence. The patients’ medication refills for each medication class will be recorded from Salamtak (including records from private and governmental pharmacies) at each follow-up visit.

1. Regimen Non-persistence Possession Ratio (RNP)

In addition to the MPR calculation, we will estimate the regimen non-persistence (RNP) or days without medication for each regimen (diabetic, hypertensive, and antihyperlipidaemic regimens) the patient had during the study [48], calculated as the total number of days the patient did not receive one or more medications for any of the patient’s chronic regimen divided by the total follow-up days.

$$\text{RNP}\text{ }\text{=}\frac{\sum\text{Days of supply of medication in a regimen}}{\text{Days of follow-up period}}$$

1. Medication Adherence Questionnaire

A validated medication adherence questionnaire translated into Arabic, showing sufficient reliability with adequate internal consistency, will be used initially to measure medication adherence at baseline for all study participants, and subsequently at each follow-up visit in the intervention group and again at the study exit (Appendix 3)[41].

The questionnaire contains four medication adherence questions from the validated Arabic version of the tool: 1) “Do you ever forget to take your medicine?” and 2) “Are you careless at times about taking your medicine?”, 3) “When you feel better do you sometimes stop taking your medicine??”, 4) “Sometimes if you feel worse when you take the medicine, do you stop taking it?”.

The total score of the medication adherence questionnaire included the first four questions with scores ranging from 0 and 4, with “Yes” having score = 1 and “No” = 0. Increased levels of adherence correspond with lower scores. Patient scores from 3 to 4 will be classified as low adherence, moderate adherence (score from 1 to 2), and high adherence (score = 0, with no answers with yes) [49] (Table 1).

Table 1: Medication adherence questionnaire scoring scheme

| Adherence questionnaire scores |
| --- |
| High adherence = 0 item answered “Yes” |
| Moderate adherence= 1 or 2 items answered “Yes” |
| Low adherence= 3 or 4 items answered “Yes” |

1. Medication Therapy Management (MTM) Program

As a new component of the MPIP, the MTM program will be made available to the clinic’s ambulatory service for the first time, and the intervention group will receive the following interventions as part of the program:

- 1. Medication counselling and reconciliation

MTM will be effectuated during the counselling session for 15–30 min at the time of dispensing medication. Each patient interview will implement the five criteria for MTM, including medication review to optimise patient treatment as per the latest treatment guidelines, assessment of the possibility of deprescribing, evaluation of any prescribed non-formulary drugs, patient counselling, and provision of printed medication educational materials, particularly for new, high alert, and narrow therapeutic index medications from an evidence-based drug reference to ensure the safe and proper use of these drugs (Lexicomp Online) (Appendix 4).

Moreover, the counselling session will include counselling on potential drug-drug or drug-food interactions and the proper use of any device or over-the-counter (OTC) medication the patient was using. Any detailed disease information or drug modifications required will be discussed and resolved by the treating physician.

Medication reconciliation and chart review will be carried out through the Salamtak local network, integrated with all governmental hospitals, ambulatory clinics, and private institutes in the Emirates of Abu Dhabi in the UAE.

The number and type of pharmacy clinical interventions, in addition to antihyperglycaemic deprescribing, will be analysed and compared between the two groups at the end of the follow-up period.

- 1. Patient Medication Booklet

A pocket-sized patient-specific medication booklet will be provided to each participant in the intervention group (Appendix 5). This initiative in the MPIP aims to promote medication adherence in elderly patients and those with low digital skills. Moreover, the booklet helps to track OTC drugs or herbal medications bought from community pharmacies and enables patients as well as community pharmacists to fill in the name of the drug and the dose by hand, which are then manually added to the patient’s medical record in Salamtak at the next MPIP visit.

During the counselling session, the counselling pharmacist will attach the prescribed medication labels to the booklet and will ensure that the booklet is filled with an updated list of all prescribed medications, medication doses, allergies, next scheduled refill, and any OTC drugs the patient is currently taking (Appendix 5).

Patients will be advised to bring the medication booklet to each follow-up visit to update the next refill schedule or any changes in their profiles. Moreover, it will be used as a reference during Salamtak downtime or when patients’ medical records from other private facilities are not available.

- 1. SEHA Mobile Application

Despite the fact that the SEHA mobile application [50] is accessible to all patients for download and usage, the patients often do not know how to use its features. As a new initiative in the MTM program, participants in the intervention group will receive face-to-face educational sessions for 5 minutes on the use of the SEHA mobile application, how to read the clinical information and laboratory results, extract their medication profile, add OTC medications to their medical record, and read notifications for medication approval from insurance as well as for subsequent medication refills.

The SEHA mobile application provides real-time individualised feedback, including patient access to Salamtak, laboratory test results, radiology reports, medications, allergies, immunisation records, and health maintenance history for patient visits occurring in SEHA facilities. Moreover, it enables patients to request or reschedule appointments or reschedule them, and search for a healthcare facility. The application sends a short message service (SMS) to the registered mobile number for appointments, with reminder notifications to remain keep the patient informed about future or follow-up appointments.

At the end of the study, we will use the SEHA mobile, and booklet use questionnaire to record the number of participants in each group using the application on their mobile device and the extent of application utilisation (Appendix 6). The results will be correlated with medication adherence to measure the effect of online technology on medication management.

